# The effectiveness of Technology-assisted Cascade Training and Supervision of community health workers in delivering the Thinking Healthy Program for perinatal depression in a post-conflict area of Pakistan – study protocol for a randomized controlled trial

**DOI:** 10.1186/s13063-016-1308-2

**Published:** 2016-04-06

**Keywords:** Thinking Healthy Program, Conflict settings, Community health workers, Technology-assisted Cascade Training and Supervision, Psychosocial intervention, Perinatal depression, Low and middle income countries

## Abstract

**Background:**

Rates of perinatal depression in low and middle income countries are reported to be very high. Perinatal depression not only has profound impact on women’s health, disability and functioning, it is associated with poor child health outcomes such as pre-term birth, under-nutrition and stunting, which ultimately have an adverse trans-generational impact. There is strong evidence in the medical literature that perinatal depression can be effectively managed with psychological treatments delivered by non-specialists. Our previous research in Pakistan led to the development of a successful perinatal depression intervention, the Thinking Healthy Program (THP). The THP is a psychological treatment delivered by community health workers. The burden of perinatal depression can be reduced through scale-up of this proven intervention; however, training of health workers at scale is a major barrier. To enhance access to such interventions there is a need to look at technological solutions to training and supervision.

**Methods/design:**

This is a non-inferiority, single-blinded randomized controlled trial. Eighty community health workers called Lady Health Workers (LHWs) working in a post-conflict rural area in Pakistan (Swat) will be recruited through the LHW program. LHWs will be randomly allocated to Technology-assisted Cascade Training and Supervision (TACTS) or to specialist-delivered training (40 in each group). The TACTS group will receive training in THP through LHW supervisors using a tablet-based training package, whereas the comparison group will receive training directly from mental health specialists. Our hypothesis is that both groups will achieve equal competence. Primary outcome measure will be competence of health workers at delivering THP using a modified ENhancing Assessment of Common Therapeutic factors (ENACT) rating scale immediately post training and after 3 months of supervision. Independent assessors will be blinded to the LHW allocation status.

**Discussion:**

Women living in post-conflict areas are at higher risk of depression compared to the general population. Implementation of evidence-based interventions for depression in such situations is a challenge because health systems are weak and human resources are scarce. The key innovation to be tested in this trial is a Technology-assisted Cascade Training and Supervision system to assist scale-up of the THP.

**Trial registration:**

Registered with ClinicalTrials.gov as GCC-THP-TACTS-2015, Identifier: NCT02644902.

## Background

The prevalence of maternal depression in low and middle income countries (LMICs) ranges between 18 and 25 % [1]. In Pakistan the mean prevalence of depression is 33 %, with women being at a greater risk than men [2]. Untreated depression in women is of particular concern due to its adverse effects on the health of the mother and infant. Maternal depression, is linked with pre-term birth [3], low birth weight [3], under-nutrition in the first year of life [4], higher rates of diarrhea [5], and early cessation of breastfeeding [6]. Maternal depression has a profound adverse trans-generational impact [6]. The economic burden of depression in pregnant and postnatal women not only includes the cost of treating depression, but the cost of complications, such as pre-term birth and low birth weight [3]. Children of depressed mothers also have higher lifetime medical spending due to the adverse effects of postpartum depression on the child’s own health [7]. The scope and magnitude of the problem is magnified in humanitarian crisis settings [8].

Evidence-based interventions for depression exist [9] but there is slow progress in the “know-do gap”: the gap between what is known and what gets implemented in LMICs [10, 11]. The burden of illness can be reduced by narrowing this gap through scale-up of proven interventions. The Thinking Healthy Program (THP) is a culturally adapted [12] cognitive behaviour therapy (CBT)-based psychosocial intervention for maternal depression, which relies on CHWs called Lady Health Workers (LHWs) for its delivery [12, 13]. In a recent meta-analysis [9], THP was shown to have one of the largest effect sizes and has been adopted by the World Health Organization (WHO) for global dissemination through its mental health Gap Action Program (mhGAP) [14].

The major issues in scaling up the coverage of health interventions include the costs, equity and quality concerns and service delivery issues [15]. In the context of scaling up, the supply of additional human resources is a major barrier [16]. Another challenge in the scaling up of this evidence-based intervention is the provision of training and supervision at scale, especially in post-conflict areas with weak health systems. We aim to meet this challenge by providing technology-based solutions to training and supervision. Building on our previous work in this area, we aim to develop a Technology-assisted Cascade Training and Supervision for the THP (TACTS-THP) system that includes a tablet-based multimedia manual, using “Avatar” characters, allowing standardized training to be delivered without the need for a specialist trainer; and a cascade training model whereby specialists supervise the LHW program supervisors from a distance, who in turn supervise the LHWs as part of their routine. The cascade training has been found to be effective in training non-specialists to deliver mental health interventions [17].

The LHW program covers 85 % of Pakistan’s rural population by utilizing 115,000 LHWs. If we are able to provide a technological solution to their training and supervision, LHWs have the potential to provide treatment to one in four women with perinatal depression in rural Pakistan. The THP-TACTS system will be widely disseminated. If proven effective the technology has the potential to be replicated for scale-up of other mental health interventions.

### Primary objective

The primary objective of this trial is to demonstrate whether LHWs in Pakistan attain the same competence level for delivering THP to depressed mothers if they are trained with the help of technology versus training by specialists.

### Secondary objective

The secondary objectives of this trial are the assessment of feasibility and acceptability of the technological training and supervision approach by LHWs and community.

### Hypothesis

LHWs trained through TACTS will be as competent in the skills needed to deliver THP as those trained by specialists.

## Methods/design

### Design

The study is a non-inferiority, single-blinded randomized controlled trial with two arms, comparing the effectiveness of two training strategies for the THP. Consolidated Standards of Reporting Trials (CONSORT) guidelines [18] will be followed in the design, implementation and reporting of this randomized controlled trial.

### Settings

We intend conducting the study in the Swat district in Northern Pakistan which has been affected by multiple humanitarian crises in recent years. Swat has a population of 1,257,602 persons, 86 % of whom live in rural areas with the average household size of 8.8 persons with a low female literacy. The resurgence of the Taliban movement in the Swat Valley of Pakistan since 2004, and the military operations in 2009 and the displacement of residents has created a humanitarian crisis in the area [19]. The devastating floods of 2010 led to thousands of people losing of their homes, and caused destruction to houses, roads, schools and health facilities [20, 21]. A recent community-based cross-sectional survey of 349 pregnant women in Swat showed that the prevalence of current psychological distress was 38.1 % [22]. Mental health impacts of conflict are often severe [8, 23] and may not be depicted in the national statistics. The health infrastructure of a post-conflict zone like Swat is particularly fragile with the health workers under threat of being attacked, thus compromising their training and supervision. The district has a functioning LHW program and LHWs, who have 10–14 years of education and provide preventive primary care services in the community, have the capacity to use technology. A Lady Health Supervisor (LHS) supervises 15–20 LHWs in one supervisory zone.

### Participant recruitment

The LHW program will be approached in the Swat district of Pakistan to obtain a list of the LHSs and LHWs who are currently working in the six LHS supervisory zones. Since Swat has extreme winter weather making some parts inaccessible in winters, the supervisory zones will be selected on the basis of accessibility throughout the year. The LHW program will be asked to inform all the LHSs and LHWs in the zones about the study. By simple random sampling 80 LHWs will be selected for the study and written informed consent will be obtained by the research team from the LHWs.

### Sample size estimation

The primary outcome of the study is the mean competence scores post training and at 3 months. We define non-inferiority as a difference of 5 points or less (corresponding to a 10 % difference on the outcome measure score) in the mean competence score between the two groups. A sample size of 80 LHWs (40 LHWs per arm) will have 99 % power to detect a 5-point margin with a 0.05 one-sided alpha level. Even after potential attrition in this area, at 3 months we will need 30 health workers in each group for a power of 80 % and a two-sided alpha error of 0.05.

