#### Contamination

The THP group supervision for LHWs will be held monthly, in addition to their routine monthly meeting. The LHWs will be advised not to disclose information to their colleagues.

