#### Statistical analysis

The competence scores of the two groups will be compared using Student’s *t* test post training and at 3 months. A difference of less than 5 points between the two groups will be interpreted as supporting the non-inferiority hypothesis. We will also examine whether the competence scores improve at the 3-month mark after supervision. Stata software will be used for this. Qualitative data will be analyzed using framework analysis and manual software for qualitative studies. Cost-effectiveness will be assessed by combining costs with the primary outcome measure in incremental cost-effectiveness analysis. In addition, repeat re-sampling from the costs and effectiveness data (bootstrapping) will be used to calculate the probability that each of the training methods is the optimal choice, subject to a range of possible maximum values (ceiling ratio) that a decision-maker might be willing to pay for a unit improvement in ENACT score. A cost-effectiveness acceptability curve will be presented by plotting these probabilities for a range of possible values of the ceiling ratio [26].

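### Competence is primary at two time points under one success rule that does not say whether non-inferiority is needed at one, either or both

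*Protocol article*

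**What the plan says.** Under Sample size estimation the protocol article states: "The primary outcome of the study is the mean competence scores post training and at 3 months". The abstract likewise places the primary measure "immediately post training and after 3 months of supervision". The two scores come from different settings. According to Outcome measure, the first is rated on standardized role plays and the second during home visits.

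Under Statistical analysis: "The competence scores of the two groups will be compared using Student’s *t* test post training and at 3 months". The success rule follows once: "A difference of less than 5 points between the two groups will be interpreted as supporting the non-inferiority hypothesis". It names no time point. Neither do the primary objective, the hypothesis or the margin as given under Primary outcome.

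Sample size estimation has two power statements. The first reads "A sample size of 80 LHWs (40 LHWs per arm) will have 99 % power to detect a 5-point margin", "with a 0.05 one-sided alpha level", and names no time point. The next sentence concerns 3 months: 30 per arm are needed for 80% power at a two-sided 0.05.

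**The concern.** With two primary results and one rule, the plan gives no verdict when one time point meets the margin and the other does not. Disagreement is plausible, because the assessment setting changes, fewer LHWs may remain at 3 months, and the protocol itself expects scores to rise with practice.

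The missing rule matters in two ways. If a claim at either time point counts, the trial has two chances at one conclusion and the error rate is no longer the stated one. If both are needed, the chance of success is lower than the headline 99%. A choice made after the data are seen could favour whichever result succeeded.

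**Working it through.** **Inputs.** From Sample size estimation: margin 5 points; 40 per arm, one-sided 0.05, power 99%; 30 per arm at 3 months, two-sided 0.05 (0.025 per side), power 80%. Assumed, because the article does not give it: the correlation r between the two test statistics, shown from 0 to 0.9. No SD is given either.

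**The plan's own power figures.** Without an SD they cannot be reproduced directly. Solving for the SD at a true difference of 0:

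SD = 5 / [√(2/n) × (z₁₋α + z_power)]

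- 40 per arm: 5 / [0.2236 × (1.645 + 2.326)] = 5.63
- 30 per arm: 5 / [0.2582 × (1.960 + 0.842)] = 6.91

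Each figure is attainable, but at different SDs. The SD may differ at 3 months because the setting differs; the article does not say.

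**Reading 1: either time point suffices.** Take a true deficit of exactly 5 points at both times. Then P(at least one false claim) = α₁ + α₂ − P(both), with P(both) from a bivariate normal. With independence this equals 1 − (1 − α₁)(1 − α₂):

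- Protocol's own levels: 1 − 0.95 × 0.975 = 0.0738
- One-sided 0.05 twice: 1 − 0.95² = 0.0975

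| r | 0.05 then 0.025 | 0.05 twice |
|---|---|---|
| 0 | 7.4% | 9.75% |
| 0.3 | 7.1% | 9.3% |
| 0.5 | 6.8% | 8.8% |
| 0.7 | 6.3% | 8.0% |
| 0.9 | 5.5% | 6.8% |

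**Reading 2: both required.** A false claim needs success at a time point where the deficit is at or beyond the margin, so its probability cannot exceed the level used there, which is at most 5%. There is no inflation.

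Joint power from the stated 99% and 80%, whatever the correlation:

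- Lower bound: 0.99 + 0.80 − 1 = 0.79
- Independence: 0.99 × 0.80 = 0.792
- Upper bound: min(0.99, 0.80) = 0.80

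This applies if only 30 per arm remain at 3 months. It also takes the two stated figures at face value. If one SD held at both times, power would be as follows:

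| SD | 40 per arm, one-sided 0.05 | 30 per arm, two-sided 0.05 | Both, if independent |
|---|---|---|---|
| 5.63 | 99.0% | 93.0% | 92.1% |
| 6.91 | 94.4% | 80.0% | 75.5% |

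**The case against.** The strongest reply is that the time points are joined by *and*, which can be read as requiring both; then no alpha adjustment is needed. The ordering of several primary analyses is also often left to the SAP, which is not shown. The first part stands as far as it goes: the article never says that either suffices, and a reader who infers this goes beyond the text. But it never says that both are needed either. The second part does not dispose of the point. The article does state a success criterion, and that criterion gives no answer when the two results differ.

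Four stronger readings are tempting, and the documents do not support them.

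- *The error nearly doubles.* 9.75% is a ceiling. It needs success at either, independence, and one-sided 0.05 at both times. The protocol gives a two-sided level at 3 months, and the same LHWs are scored twice, so some correlation is likely.
- *The power statement leaves out 3 months.* It does not: 80% is given for that time. Only the power of the combined claim is missing.
- *The error is far larger because the rule uses the observed difference.* Read literally, such a rule errs 50% of the time at a true 5-point deficit even at a single time point. The step to 75% for either, if independent, is the only part due to having two time points. The rest is a separate defect.
- *Contamination lets the diluted 3-month comparison rescue a failed first one.* The article offers only a precaution, "The LHWs will be advised not to disclose information to their colleagues". That both arms meet in the same zones is an inference from individual allocation across six zones, and nothing establishes that the first score is free of contamination.

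**Conclusion.** The point holds as a badly fixed success criterion. There are two primary time points, a test at each, and one rule that does not say how the results combine.

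Its size depends on the reading. If either suffices, the false-claim risk is about 5.5% to 7.4% at the protocol's own levels for correlations from 0.9 down to 0, and at most 9.75% with one-sided 0.05 twice. If both are required, the error stays at or below 5%, and the stated figures imply joint power of about 79% to 80%, which the article does not give. The error figures assume a true deficit at the margin at both times and approximately normal test statistics. The joint power assumes a true difference of zero and 30 per arm at 3 months.

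This should be settled before enrollment. It does not show that the trial is underpowered or that a claim on either time point is intended.

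**What to change.** Before enrollment, which the Trial status section says has not started, adopt one of two rules.

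1. **Fixed sequence at full alpha.** State the order in advance, and test the second time point for non-inferiority only if the first succeeds. Either order is defensible: the role play is standardized and can use the full sample, while the live observation reflects supervision and actual delivery.
2. **Both required.** Say so, and state the joint power.

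Under either rule, state one alpha level and sidedness for both times, base each test on the confidence limit for the difference against the 5-point margin, and report the conclusion and the power by time point.

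The cost is a few sentences and no added participants. Under the first rule, no non-inferiority claim is possible at the second time point if the first fails. Under the second, the stated power drops to about 79% to 80% on the protocol's own figures.

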### Randomization

The selected LHWs will be randomly allocated to the technology experimental arm or the specialist group control arm. Randomization will be conducted by an individual not involved in the study by using computer-generated random numbers (Fig. 1).

**Fig. 1 Fig1:**
[figure not shown]
Randomization for Think Healthy Program-Technology-assisted Cascade Training and Supervision (THP-TACTS)

### The intervention – TACTS

A tablet-based multimedia manual is developed for THP training and supervision purposes. The intervention material is divided into five training sessions, which are converted into narrative scripts by a panel of THP experts. The narratives have incorporated all the core techniques and principles of the intervention such as effective use of counseling skills, collaboration with the mothers’ families, guided discovery (style of questioning to probe mother’s health beliefs), and setting health-related tasks. Culturally appropriate real-life characters for the trainers and the trainees have been developed. An artist has converted the characters into “Avatars” (graphic image representing each character) (Fig. 1), which were used to voice the narrative scripts. Our group had successfully used this methodology of Technology-assisted Cascade Training (TACT) for training parents of children with developmental disorders [22]. The TACTS has also used case scenarios and role plays to reinforce key messages and training skills. For example, the role plays have demonstrated: sessions’ delivery by THP-trained LHWs to depressed mothers, dealing with challenging situations and dealing with adverse events. The training has been made interactive through suggesting activities for the actual trainees using a pause button and instructions. These activities are aimed to help them practice delivery of sessions through the role plays, peer assessment of role plays, reflecting on one’s learning, sharing relevant personal and work experiences, and practicing problem-solving strategies. A separate module on supervision has been developed for the LHSs to guide them on conducting supervisions. The software has the provision to modify and update the training scenarios. The software will be tested with LHSs and academics during and after the development process. The qualitative feedback regarding multiple aspects of the system and the user interface will be recorded.

In the intervention arm THP trainers (who have experience of delivering THP for 1 year) will give 5 days’ training to the LHS on THP-TACTS and will supervise three practice cases delivered by the LHSs. The LHSs will then cascade this training using THP-TACTS to train LHWs in 5-day training sessions (Fig 2).

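### TACTS trainees are nested within Lady Health Supervisors who train and supervise them, but the t test and the power statement treat all 80 LHWs as independent

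*Protocol article*

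**What the plan says.** **Allocation.** Individual LHWs are randomised (Randomization): "The selected LHWs will be randomly allocated to the technology experimental arm or the specialist group control arm". They are drawn from those "currently working in the six LHS supervisory zones" (Participant recruitment). Settings describes one LHS overseeing 15–20 LHWs in a zone.

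**Delivery.** In the TACTS arm, THP trainers prepare the LHSs, and then "The LHSs will then cascade this training using THP-TACTS to train LHWs in 5-day training sessions" (The intervention – TACTS). The Background adds that LHSs, themselves supervised from a distance by specialists, supervise the LHWs in their routine work. Supervision is in groups (Contamination): "The THP group supervision for LHWs will be held monthly, in addition to their routine monthly meeting". Control LHWs are trained directly by specialists; the article does not say how many specialists or training groups there are.

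**Analysis and power.** Under Statistical analysis, "The competence scores of the two groups will be compared using" Student's t test, after training and at 3 months. A difference below 5 points is read as supporting non-inferiority, and no confidence limit is named. Under Sample size estimation, "A sample size of 80 LHWs (40 LHWs per arm) will have 99 % power to detect a 5-point margin with a 0.05 one-sided alpha level". A fallback of 30 per group is given for 80% power at two-sided 0.05. Neither statement has an SD, an ICC or a design effect.

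**The concern.** Randomising individuals makes the arms comparable at baseline, but it does not keep outcomes independent afterwards. Once an LHS has trained and supervised a group, her skill shifts all their scores together. The t test assumes that this does not happen. The result is a partially nested design, with clustering by LHS in the TACTS arm and possibly by specialist or training group in the control arm.

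In a non-inferiority trial, a standard error that is too small favours the trial's own hypothesis. The variation being ignored also bears on the research question, because the trial asks whether training cascaded through LHSs can stand in for training by specialists. An interval that leaves out between-LHS variation speaks only for the particular LHSs who took part.

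This is not a detail left to an analysis plan. The article names the primary test, and its own delivery model breaks that test's independence assumption.

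**Working it through.** **Inputs.** From the article: 40 LHWs per arm; margin 5 ENACT points; one-sided alpha 0.05 with 99% power; fallback of 30 per group, two-sided 0.05, 80% power; six zones. Inferred: one LHS per zone, hence six LHSs, all training groups of similar size. Assumed: ICC 0.02, 0.05, 0.10 and 0.20, in the TACTS arm only.

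**1. The stated power.** It cannot be reproduced directly because no SD is given. Solving for it with SD = 5·√(n/2)/(z_alpha + z_power):

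- 99%, n = 40, one-sided 0.05: 5·√20/(1.645 + 2.326) = 5.63 (5.58 by noncentral t).
- 80%, n = 30, two-sided 0.05: 5·√15/(1.960 + 0.842) = 6.91 (6.80 by noncentral t).

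One SD does not yield both figures: 5.63 would give 93.0% at 30 per group, and 6.91 would give 94.4% at 40 per arm. Each is used below only with the claim it came from.

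**2. False non-inferiority at 40 per arm.** Group size m = 40/6 = 6.67. Design effect in the TACTS arm: DE = 1 + (m − 1)·ICC. The variance of the difference is multiplied by F = (1 + DE)/2. The true one-sided error of a nominal 5% test is 1 − Φ(1.645/√F).

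| ICC | DE | √F (true SE ÷ t-test SE) | Error, formula | Error, simulated |
|---|---|---|---|---|
| 0 | 1.00 | 1.00 | 5.0% | 4.9% |
| 0.02 | 1.11 | 1.03 | 5.5% | 5.5% |
| 0.05 | 1.28 | 1.07 | 6.2% | 6.3% |
| 0.10 | 1.57 | 1.13 | 7.3% | 7.3% |
| 0.20 | 2.13 | 1.25 | 9.4% | 9.6% |

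The simulation used 200,000 trials per ICC, TACTS groups of 7, 7, 7, 7, 6 and 6, a Student's t test on 78 df, and a true deficit equal to the margin.

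Two sensitivities:

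- If control training groups cluster in the same way, F = DE and the error is 7.3%, 9.4% and 13.0% at ICC 0.05, 0.10 and 0.20.
- If only three LHSs trained, m = 13.3. At ICC 0.10, DE = 2.23, √F = 1.27 and the error is 9.8%.

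**3. Power at 40 per arm.** Power = Φ(5/SE − 1.645), with SE = 5.63·√(2/40)·√F = 1.259·√F. At ICC 0 this returns 99.0%. At ICC 0.02/0.05/0.10/0.20 it gives 98.7%/98.1%/96.9%/93.7%.

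**4. Power at 30 per group.** m = 5, so DE = 1.08/1.20/1.40/1.80 and F = 1.04/1.10/1.20/1.40. With SD 6.80, SE = 6.80·√(2/30)·√F = 1.756·√F. Noncentral t on 58 df, two-sided 0.05, gives 80% at ICC 0 and 78.4%/76.1%/72.5%/65.8% at the four ICCs. Steps 3 and 4 do not count the further loss from having few trainers.

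**5. Does a clustered analysis repair it?** In the same simulation, LHS means were compared with individual controls using Satterthwaite df. The error stayed at about 5.1%. Power at SD 5.63 was 98%/97%/95%/90% for ICC 0.02/0.05/0.10/0.20.

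**The case against.** **The stated rule is not a test.** Read literally, Statistical analysis compares the observed difference with 5 points. False non-inferiority at the margin is then about 50% whatever the ICC. This stands: the error figures above apply only if a t-based test or confidence limit decides. The literal rule is a separate defect, however, and replacing it with a limit from the planned t test would still give a limit that ignores clustering.

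**The size is assumed.** The article gives no ICC. TACTS uses a standardised multimedia manual, so a small ICC is plausible, though not shown. At 0.02 the error is only 5.5%. This stands as to size, but not as to direction.

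**The number of LHSs who train is not stated.** Nor does the article say whether each trains only her own LHWs. Six is an inference from Settings and Participant recruitment. Fewer trainers would make the problem worse.

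**Power is hardly touched at 40 per arm.** Correct. A reader might infer that the 99% claim collapses; with the SD it implies, it does not.

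**Stratification and zones.** A reader might also infer that allocation is unstratified by zone and that zone differences make the standard error too small. The article supports neither. It mentions computer-generated random numbers and a figure that is not shown, and silence on stratification is not evidence of its absence. Because LHWs are randomised individually, zone differences that exist beforehand are shared by both arms and, under simple allocation, already lie within the variance the t test estimates. Only the trainer or group effect that arises after randomisation is at issue.

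**Conclusion.** The point holds in a limited form. The TACTS arm is nested within LHSs by design, and both the named test and the power statement ignore this. The direction is certain for any positive trainer-level ICC: the standard error is too small and non-inferiority too easy to claim. For ICC 0.02 to 0.20, a nominal 5% one-sided error becomes about 5.5% to 9.4%. The loss of power is small at 40 per arm (99% to about 94% at worst) and larger at the 30-per-group fallback (80% to about 66% at worst).

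These sizes rest on an assumed ICC, six inferred trainers, clustering in the TACTS arm only, and a t-based test or confidence limit as the decision rule. They show a modest distortion that should be corrected; they do not show that the trial cannot answer its question.

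**What to change.** 1. Record for every LHW the LHS, or specialist, and the group in which she was trained and supervised.
2. Replace the t test with a partially nested analysis: a random LHS or training-group effect in the TACTS arm, and in the control arm too if it has more than one training group, with small-sample degrees of freedom.
3. Take the confidence limit from that analysis and compare it with the 5-point margin.
4. Restate power at 40 and at 30 per group with one stated SD, one alpha convention and a range of ICCs, and say how many LHSs will train.

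Zone stratification is at most an optional gain in precision and is not needed to repair this point.

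The cost is an extra identifier and a few lines of analysis code. The interval will be somewhat wider and the quoted power lower. With about six trainers the between-LHS variance will be poorly estimated, which is why the small-sample degrees of freedom matter. Trial status says that enrolment has not started, so all of this can be set in advance.
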